### 1.2. Public Involvement Statement

The feasibility trial was co-designed with people living and working in farming communities, as reported previously [19]. Peer worker training and trial design were heavily influenced by feedback from the co-design process and ongoing community consultation. For example, local strategies for recruitment of peer workers and trial participants were informed by a Community Reference Group. Lived experience researchers are also part of the investigator team and have decision-making authority over the conduct of the trial.

## 2. Methods

### 2.1. Trial Design

A single-blind (researcher), parallel group, 1:1 allocation, randomised controlled feasibility trial using the Australian Teletrial Program [21] teletrial model—a group of study sites working together to conduct a clinical trial.

### 2.2. Trial Setting

Based on Behavioural Activation, Back-on-Track is a community-based intervention that is delivered by peer workers in a participant’s home, their workplace (e.g., the farm), a mutually agreed public location, or via online video call (Zoom or the healthdirect [22] Video Call service). Participants will be recruited from three dairy farming regions in rural Victoria, Australia. Whilst the trial is located in dairy farming regions, participants do not need to be dairy farmers per se.

### 2.3. Eligibility Criteria (Peer Workers)

People aged over 18 years with lived experience living or working in a rural farming community will be eligible to apply to be peer workers. Peer workers may have personal experience of mental stress or distress, or previous mental ill-health. However, this is not an inclusion criterion for this trial.

### 2.4. Recruitment (Peer Workers)

Peer workers will be recruited by the following means:(i)Inviting expressions of interest from people living in the local communities we are seeking to recruit from (e.g., advertising via local industry newsletters, social media, and flyers).(ii)Direct approach from Community Reference Group members in the local communities we are recruiting from.(iii)Advertisement of peer worker positions more broadly through National Centre for Farmer Health networks, including social media and monthly newsletters.

Peer workers will be employed by Western District Health Service, which provides primary, secondary, and tertiary health care in rural Australia. They will be employed on a casual contract as complementary therapy workers and will complete standard requirements of employment by Western District Health Service (e.g., pre-employment interview, reference checks, pre-employment medical check, police check, Working with Children Check, workplace competencies). Peer workers will also be required to complete a Participant Information and Consent Form (PICF).

All employment costs associated with the trial (training, police check, working with children check, travel) will be reimbursed through the project grant.

### 2.5. Eligibility Criteria (Participants)

Forty farming community members (participants) with depression will be recruited.

#### 2.5.1. Inclusion Criteria

Over 15 years of age.A Patient Health Questionnaire (PHQ-9) score of between five and 19.A member of the farming community (farm owners and managers, farm workers, members of farming families, members of agriculture-dependent communities) within geographic proximity of the three target farming regions.

#### 2.5.2. Exclusion Criteria

Commenced any medication for the treatment of depression in the past 4 weeks.Current psychological (e.g., Cognitive Behavioural Therapy) treatment for a mental health condition.Previous treatment with Transcranial Magnetic Stimulation or Electroconvulsive Therapy for depression.Medically confirmed diagnosis of psychosis, personality disorder, or cognitive impairment.Serious long-term health condition that may necessitate hospital admission or regular contact with secondary health services during the trial.Active suicidality or report of a suicide attempt in the past 2 months.

### 2.6. Interventions

#### 2.6.1. Experimental (Back-on-Track)

Back-on-Track is a 10-session psychological intervention based on Behavioural Activation. The intervention is focused on initiating and/or reinstating activities which are meaningful to them by scheduling activities, monitoring behaviours, and identifying where changing these behaviours and activities may be beneficial to improving their mood. Throughout the intervention, participants will be asked to complete worksheets and engage in discussion with their peer workers to assist with monitoring these activities and behaviours.

##### Peer Worker Training

Peer workers will complete the University of South Australia Professional Certificate in Behavioural Activation for Depression [23]. This course will enable peer workers to practice key Behavioural Activation skills, including the following:Teaching people to acquire the skills to monitor their mood.Helping individuals recognise the relationship between behaviours and their impact on mood.Supporting individuals to develop skills to minimise avoidance and rumination behaviours that may negatively impact mood.Assisting people to schedule behaviours/activities that may enhance mood.

Behavioural Activation training typically takes around 56 h to complete, divided into a series of four modules that can be completed over a 3-month period. Whilst a substantial commitment for trainees, we have calibrated that this is the required amount of time necessary to ensure peer workers are able to deliver Behavioural Activation with a high degree of fidelity to model.

We anticipate that by utilising an asynchronous Behavioural Activation platform, this will enable us to provide training at-scale to peer workers within the context of a definitive trial and subsequent implementation strategy.

Peer worker competency to deliver Behavioural Activation will be demonstrated through expert review of three video recordings demonstrating the application of Behavioural Activation by peer workers in a simulated session. Each recording will focus on different Behavioural Activation skills, including mood monitoring, recognising behavioural patterns, and activity scheduling.

Peer workers will receive a further 20 h of skills training focused on the following:Rationale for peer delivered interventions.Overview of depression and treatments, including differences in presentations between young people and adults.Effective communication.Confidentiality.Working safely with people at risk of suicide.Peer worker self-care and safety.Dealing with difficult situations.Conflicts of interest.Referral pathways for participants at risk.

The full training package takes approximately 76 h to complete and peer workers will need to pass the standardised competency assessment to successfully complete the training. During delivery of the intervention, peer workers will receive fortnightly online group supervision with a clinical psychologist and Behavioural Activation specialist to support them whilst working with participants.

#### 2.6.2. Control (Managing Stress on the Farm)

Participants allocated to the control intervention will receive treatment as usual (primary care visits, antidepressant medication if indicated), weekly mood monitoring, and guided self-help (Managing Stress on the Farm), representing the standard first-line treatment option for people with depression. An automated email directing participants to complete their mood rating will be sent weekly along with a reminder SMS sent to their mobile phone. The workbook provides tailored information, practical activities, and links to further resources (including what to do in a crisis) to support the mental health of members of the farming community. A weekly ‘check-in’ addresses some of the attentional issues related to a self-help workbook control intervention.

An attentional control—to address the non-specific effects of the experimental intervention—was discussed as an alternative comparator intervention. Although there are methodological advantages, we did not consider an attentional control to be consistent with our ethical obligation to ensure that participants were receiving standard of care (guided self-help). That said, we acknowledge the potential that this may overestimate the acceptability of the Back-on-Track intervention.

### 2.7. Outcomes

Outcome measures will be administered at baseline (week 0) and at weeks 10 and 26 follow-up. The primary outcome (to be used in a definitive trial) is depressive symptoms determined by change in PHQ-9 scores [24]. The PHQ-9 is a self-administered measure of depression symptoms that has been extensively used in clinical trials of psychological treatment.

Secondary outcomes (proposed) are as follows:Enhanced work performance—determined using the Work Productivity and Activity Impairment questionnaire [25], a six-item validated instrument to measure impairments in both paid work and unpaid work.Reduced loneliness—determined using the University of California, Los Angeles (UCLA) loneliness scale [26], a 20-item validated scale designed to measure the participant’s subjective feelings of loneliness as well as feelings of social isolation.Enhanced overall wellbeing—determined using the WHO-5 Wellbeing index [27], a short self-reported measure of current mental wellbeing.Improved overall quality of life—determined using the AQoL-4D [28], a validated, health-related multi-attribute utility instrument.

Outcome measures are estimated to take a total of 20 min to complete. For noting, we will not conduct or report any form of statistical analysis to determine the efficacy of the Back-on-Track intervention.

### 2.8. Treatment Fidelity

Treatment fidelity will be determined using the Behavioural Activation fidelity assessment—found to be reliable, feasible, and acceptable in previous studies [20]. A random sample (approximately 20, 10%) of all sessions conducted during the trial will be recorded using Zoom. At the end of the trial, they will be blind rated by an independent (not part of the research group) clinician experienced in Behavioural Activation. A 10-percent sample, for the purposes of fidelity checking, is typical in trials of novel psychological treatments. Peer workers will need to be rated as three (moderately) or higher against each of the 10 items of the Behavioural Activation fidelity assessment (a total score ≥ 30). Fidelity ratings will not be completed until after the treatment has concluded; consequently, it will not be possible to provide feedback to peer workers whilst treatment is ongoing, which is an acknowledge limitation of our fidelity-monitoring procedure.

Providing consent for audio recording of sessions will be part of the participation consent process, but not compulsory. Participants will have the option to indicate that they do not want sessions to be recorded.

### 2.9. Economic Data

Costs—including the cost of training and delivering the intervention (Back-on-Track) and the cost of the control (Managing Stress on the Farm self-help workbook)—will be calculated. Identified costs for the Back-on-Track intervention will include peer worker training, training materials, peer supervision (e.g., clinical psychologist time), staff co-ordination, administrative overheads, and delivery time per participant. For the control group, identified costs will include components of treatment as usual (e.g., GP visits and antidepressant prescriptions where indicated), the provision of the guided self-help materials, and automated weekly mood monitoring.

Additionally, healthcare service use data will be collected throughout the trial period including Medicare Benefits Schedule (MBS—primary care attendance), Pharmaceutical Benefits Scheme (PBS—prescribed medications via Services Australia), and the Victorian Admitted Episodes Dataset (VAED) via Victorian Agency for Health Information (VAHI) for emergency department and inpatient hospitalisation data. Participant-level data on health service utilisation will be linked and analysed to quantify any differences in service use between the intervention and control groups, capturing both physical and mental health-related encounters.

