## 4. Economic Evaluation

The economic evaluation reporting will adhere to the Consolidated Health Economic Evaluation Reporting Standards (CHEERS) statement [35]. A cost-consequence analysis will explore the costs associated with the programme and report these alongside potential benefits and outcomes. A cost-consequence analysis (CCA) is a form of economic evaluation where costs and outcomes are listed separately rather than combined into a single metric (such as a cost-effectiveness ratio). This approach allows decision-makers to consider a range of impacts and make context-specific judgements about value and trade-offs. The analysis will be conducted from the ‘funder perspective’, allowing health care organisations to consider implementation cost for this and similar programmes.

Consequences will include the primary clinical outcome of depressive symptoms (measured by change in PHQ-9), along with secondary outcomes such as enhanced work performance (Work Productivity and Activity Impairment questionnaire), reduced loneliness (UCLA Loneliness Scale), improved wellbeing (WHO-5), and health-related quality of life (AQoL-4D). Patterns of health service use (e.g., GP visits, hospital presentations, mental health service contacts) will also be reported as a key outcome, reflecting potential shifts in demand associated with the intervention. These outcomes capture a broad range of potential programme benefits and align with the lived experience goals of the target population.

Costs and outcomes will not be aggregated into a single cost-effectiveness ratio, in line with the cost-consequence approach, but will be presented in a disaggregated format to support decision making. Sensitivity analyses will be conducted to test assumptions around intervention delivery costs and variability in health service use. In addition, outcomes such as the AQoL-4D will provide utility weights that may be used in future cost-utility analyses.

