#### 4.4.2. Distress Management Protocol

A stepped approach will be adopted to manage people experiencing distress or thoughts or plans for self-harm during the trial. All members of the research team and peer workers will receive training around the distress protocol. The peer worker programme delivery manual will include a flowchart outlining the distress protocol for ongoing referral. The participant workbook will include a flow chart outlining the process for participants to seek mental health support should distress be experienced outside of meetings with their peer worker, including direction to local supports where available. Participants will also be offered the opportunity to speak with a psychologist if they withdraw from the trial due to heightened distress.

Control group participants will also be sent weekly mood-monitoring checks. The Clinical Trials Platform will be notified if there is a decline in the mood-monitoring score for 2 consecutive weeks or if the score is less than or equal to four for 2 consecutive weeks. The Clinical Trials Platform will notify the trial psychologist, who will contact the participant to assess their mental health and make any necessary referrals.

Researchers and peer workers will follow the process as above when working with young people aged 15 to 17 years. Additionally, when young people express concern about harming themselves, parents or guardians will be informed about the identified risk.

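### Usual-care GP visits and antidepressants are listed as costs of the control arm only, which tilts the cost comparison towards Back-on-Track

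*Protocol article*

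**What the plan says.** All references are to the protocol article.

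- **Back-on-Track costs (section 2.9).** The list opens with "Identified costs for the Back-on-Track intervention will include peer worker training, training materials, peer supervision", where clinical psychologist time is the example given for supervision. It closes with "staff co-ordination, administrative overheads, and delivery time per participant". No item of usual care is named.
- **Control costs (section 2.9).** "For the control group, identified costs will include components of treatment as usual (e.g., GP visits and antidepressant prescriptions where indicated". The self-help materials and the automated mood monitoring complete the list.
- **Linked data (section 2.9).** The next paragraph adds that "healthcare service use data will be collected throughout the trial period including Medicare Benefits Schedule (MBS—primary care attendance" and, for medicines, "Pharmaceutical Benefits Scheme (PBS—prescribed medications via Services Australia". Hospital data are also to be obtained. These participant-level data are to be compared between the two arms.
- **Use in the analysis (section 4).** Costs and outcomes are listed separately, and no ratio is formed. On the consequence side, "Patterns of health service use (e.g., GP visits, hospital presentations, mental health service contacts) will also be reported as a key outcome". The closing paragraph of section 4 says that the results will shape the definitive trial's economic parameters and support a later model of cost per QALY.

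**The concern.** The two cost lists in section 2.9 are parallel, but they do not cover the same kinds of item. One holds what it costs to run the programme. The other holds what it costs to run the control package plus the participant's ordinary primary care and antidepressants. A comparison of arm costs is interpretable only if an item that can occur in both arms is costed in both arms.

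Usual care can occur in both arms. Section 2.6.2 describes it as part of the control package, but no section says that Back-on-Track participants forgo it. Section 2.5.2 excludes people who began depression medication in the four weeks before entry, so longer-standing users can enter either arm. Section 4.2 asks participants in general to report GP visits.

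At stake is the cost column of the cost-consequence table. The feasibility criteria in section 1.1 are untouched. But if the one-sided item is carried forward, the definitive trial and the later model would start from a cost difference that favours Back-on-Track for a reason of bookkeeping.

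**Working it through.** The article gives no unit costs, visit rates or cost difference, so there is no figure of the plan's own to reproduce. The check sets the two lists side by side and then uses simple algebra.

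**Items by arm, from section 2.9**

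| Item | Back-on-Track list | Control list | Linked data |
|---|---|---|---|
| Training, materials, supervision, co-ordination, overheads, delivery | yes | not applicable | no |
| Workbook, automated mood monitoring | not applicable | yes | no |
| GP visits | **no** | **yes** | both arms |
| Antidepressant prescriptions | **no** | **yes** | both arms |

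**Notation.** Let C_c and C_b be the mean cost per participant of GP visits and antidepressants in control and in Back-on-Track. Both are unknown. The true difference in this component, control minus Back-on-Track, is C_c − C_b.

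**Three readings of the text**

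1. *The lists are the cost side, and the linked data are reported only as service use.* Control is charged C_c and Back-on-Track 0, so the listed difference is C_c. Error = C_c − (C_c − C_b) = C_b, which is the usual care left out of the Back-on-Track arm.
2. *The lists are the cost side, and priced linked data are added in both arms.* Control is charged 2C_c and Back-on-Track C_b, so the difference is 2C_c − C_b. Error = (2C_c − C_b) − (C_c − C_b) = C_c, which is the control item counted twice.
3. *The linked data are the single source for this item in both arms.* Control is charged C_c and Back-on-Track C_b. Error = 0.

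**Illustration with equal use, C_c = C_b = C (assumed values, in currency units)**

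| C | True difference | Reading 1 | Reading 2 | Reading 3 |
|---|---|---|---|---|
| 100 | 0 | 100 − 0 = 100 | 200 − 100 = 100 | 100 − 100 = 0 |
| 300 | 0 | 300 − 0 = 300 | 600 − 300 = 300 | 300 − 300 = 0 |
| 1000 | 0 | 1000 − 0 = 1000 | 2000 − 1000 = 1000 | 1000 − 1000 = 0 |

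Readings 1 and 2 err in the same direction, against control. Reading 3 is free of error, but the article does not state it. Under reading 1 the error vanishes only if Back-on-Track participants use no such care.

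**The case against.** The strongest reply is that the lists are not meant to be complete. Both are introduced as what costs will include, and the control entry gives only examples. Linked service use is collected identically in both arms, and section 4 plans sensitivity analyses on delivery costs and on variability in service use. The article also condenses a fuller protocol, in which unit costs and data sources would normally be set out.

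Part of this stands. The between-arm comparison of service use from the linked data is symmetric and is not affected by the wording of the lists. For that reason a reader should not treat the cost table as the trial's only planned comparison between arms, nor call the cost difference wrong by construction: reading 3 remains open to the analyst. Details such as the precise scope of the funder perspective can fairly be left to a health-economic plan.

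The reply does not remove the point. An item named in one of two parallel lists and absent from the other is a stated costing rule, not an omitted detail. Sensitivity analyses that vary delivery costs and service use do not restore an item missing from one arm.

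A reader might also infer that the plan double counts GP visits and prescriptions. The article does not support that. It nowhere says that the linked data are priced and added to the control item, and they may be the source of that item. Showing a visit as a cost and again as service use in a disaggregated table does not sum it twice. Reading 2 is a possibility that the wording leaves open.

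**Conclusion.** The point holds in a limited form. Section 2.9 charges usual-care GP visits and antidepressants to control and not to Back-on-Track, although both arms may use them. Taken literally, this raises the control cost relative to Back-on-Track by the omitted C_b, or by C_c if priced linked data are added on top. The direction is clear whenever that care is used; the amount is unknown, because no unit costs or usage figures are given. Any monetary estimate would rest on outside assumptions. Double counting is a risk that follows from the undefined link between the control item and the linked data, and no more than that.

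A side issue does not carry the conclusion. Under section 4.4.2, when control-arm mood monitoring crosses its threshold, "The Clinical Trials Platform will notify the trial psychologist, who will contact the participant to assess their mental health", and this time appears in neither cost list. A reader might infer that control is materially under-costed for this reason. The article does not give the mood scale's properties, its variability or the number of ratings, so the frequency of such contacts cannot be stated. Whether trial safety procedures count as programme cost is a matter of convention.

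**What to change.** Revise the costing paragraph of section 2.9, and section 4 to match:

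1. Limit programme cost in each arm to what the trial adds: training, supervision and delivery items for Back-on-Track; workbook and mood monitoring for control.
2. Remove GP visits and antidepressants from the control programme list. Cost GP visits, prescriptions and hospital use once, from the linked data, with the same items in both arms, on a separate line.
3. State whether service use enters the table as a cost, as a consequence, or as both, and confirm that no use is summed twice.
4. Optionally, report the trial-psychologist contacts triggered by control-arm mood monitoring next to the costs.

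The cost is a small change of wording and the work of pricing the linked service use in both arms. The linked data are already to be collected, so steps 1 to 3 need no new data collection. Step 4 needs a simple count of contacts.

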### 4.2. Safety Monitoring

Participants will complete trial measures at three time-points: baseline (week 0), end of treatment (week 10), and follow-up (week 26). During the assessments, participants will be required to self-report any medical occurrences, GP visits, hospital admissions, or if they have been sick or unwell (physically or mentally) during the trial period. They will also be asked to report any suicidal thoughts or suicide attempts that have occurred.

An SMS will be sent to participants and peer workers every 2 weeks using REDCap (via TWILIO—a third-party web service), asking them to report any adverse events that occurred. The adverse event reporting period spans from the time of consent through to the completion of week-26 assessments. Adverse events will be graded according to the Common Terminology Criteria for Adverse Events (CTCAE) Version 5.0 [38].

Causality of adverse events will be assessed by the principal investigator to determine if there is a possible link with the trial intervention. The trial will cease immediately if there are any suicide attempts or fatalities that are plausibly linked to either the trial intervention or trial procedures. Adverse events will be reported to the trial sponsor and the relevant human research ethics committee.

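### Emergency department use is assigned to a dataset of admitted episodes, so visits that end without admission appear not to be covered by any named economic source

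*Protocol article*

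**What the plan says.** Section 2.9 (Economic Data) of the protocol article lists three linked sources of service use:

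- "Medicare Benefits Schedule (MBS—primary care attendance"
- "Pharmaceutical Benefits Scheme (PBS—prescribed medications via Services Australia"
- "Victorian Admitted Episodes Dataset (VAED) via Victorian Agency for Health Information (VAHI) for emergency department and inpatient hospitalisation data"

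The same section gives the purpose: "Participant-level data on health service utilisation will be linked and analysed to quantify any differences in service use between the intervention and control groups".

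Section 4 (Economic Evaluation) sets the status of these data: "Patterns of health service use (e.g., GP visits, hospital presentations, mental health service contacts) will also be reported as a key outcome". It also says that costs and outcomes will be shown separately, with no cost-effectiveness ratio, and that the findings will feed the design and economic parameters of a definitive trial and a longer-term model.

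Section 4.2 (Safety Monitoring) adds a second route by which some contacts may be recorded. At the assessments, "participants will be required to self-report any medical occurrences, GP visits, hospital admissions, or if they have been sick or unwell". Participants are also asked there about suicidal thoughts and attempts. A text message every two weeks asks participants and peer workers for adverse events, from consent to week 26.

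**The concern.** The outcome is wider than the source given for it. A hospital presentation includes an emergency visit that ends in discharge home. On the ordinary meaning of its title, a dataset of admitted episodes does not include such a visit. If the linkage is requested as written, the emergency line of the cost-consequence table would hold only visits that led to a stay, yet it would be labelled as emergency department use.

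This matters for two reasons. First, the trial itself points people towards this setting: section 2.12.3 has the researcher direct anyone who feels at imminent risk of harm to a GP, the Emergency Department or emergency services. Second, trying out the data sources is part of what this study is for, since section 4 says the analysis will shape the data collection and economic inputs of the next trial. An unnoticed gap in coverage would be carried forward.

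**Working it through.** The article gives no figure to reproduce. The check is whether each named source covers an emergency visit without admission.

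**Coverage, source by source**

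| Source | Where named | What the article says it covers | Emergency visit without admission? |
|---|---|---|---|
| MBS | 2.9 | primary care attendance | not described as covered |
| PBS | 2.9 | prescribed medicines | no |
| VAED | 2.9 | emergency and inpatient data; title says admitted episodes | appears not |
| Assessment self-report | 4.2 | medical occurrences, GP visits, hospital admissions, being sick or unwell | not named; might be reported as a medical occurrence |
| Two-weekly text message | 4.2 | adverse events | only if the event behind the visit is reported |

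The first three are the named economic sources, and none of them clearly covers the visit. The last two could, but they are described for safety only. Nothing in section 2.9 or section 4 brings them into the cost-consequence analysis.

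**Size of the under-count**

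Let *V* be the number of emergency visits and *a* the share that end in admission. A source limited to admitted episodes captures at most *aV*, so it misses at least (1 − *a*)*V*, a share of 1 − *a*. The article gives neither *V* nor *a*. The values below are assumptions that show only how the result moves:

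- *a* = 0.2: 1 − 0.2 = 0.8, so 80% missed
- *a* = 0.4: 1 − 0.4 = 0.6, so 60% missed
- *a* = 0.6: 1 − 0.6 = 0.4, so 40% missed

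The gap closes only at *a* = 1, when every emergency visit ends in admission.

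**Effect on the between-group description**

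The arms are of about equal size (20 each, section 2.11). With visits *V*₁ and *V*₀ and admission shares *a*₁ and *a*₀, the captured counts are *a*₁*V*₁ and *a*₀*V*₀.

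- If *a*₁ = *a*₀ = *a*, the ratio *V*₁/*V*₀ is preserved, but the difference shrinks to *a*(*V*₁ − *V*₀), and so does any cost difference built on it.
- If *a*₁ and *a*₀ differ, the ratio is multiplied by *a*₁/*a*₀ and can move either way.

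The article gives no information on which case applies.

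**The case against.** The strongest reply is that coverage is being read from a title. The article does not describe what the dataset holds, and the source list is introduced as an inclusive one. The authors clearly mean to obtain emergency data from the state agency, and naming one dataset for a two-part request may be shorthand in a condensed article, with the extract specified in the full protocol or the linkage application. This stands as a limit on certainty: the article supports saying that such visits appear not to be covered, not that they will be lost. It does not remove the point, because the article does not merely leave a source unstated. It assigns emergency use to a named dataset whose title does not fit.

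A second reply is that section 4.2 is broad. Medical occurrences, illness, suicidal thoughts and attempts are all asked about, and the text messages run throughout. Section 4.4.2 adds weekly mood monitoring, with psychologist contact, for controls. This also stands in part. A reader might infer that crises among participants would go unseen. The article does not support that, because the events behind such visits have several routes to detection. Those routes do not supply a count of emergency visits for costing, however, and none is named for that use.

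A third reply concerns scale. There are 40 participants followed for 26 weeks. Section 2.5.2 excludes active suicidality, a recent attempt and serious conditions that may need admission. Total hospital use may therefore be small. Section 4 also plans sensitivity analyses on service use. The number of missed visits may indeed be low. But a sensitivity analysis can only vary an assumption about visits that were never recorded; it cannot recover them. The exclusion of people likely to be admitted also gives no reason to expect that most emergency visits here would end in admission.

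**Conclusion.** The point holds as a source that does not match its outcome. Section 2.9 gives emergency department use to a dataset of admitted episodes, no other named economic source covers visits without admission, and section 4 reports hospital presentations within a key outcome.

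The size of the under-count is unknown. It is at least one minus the share of emergency visits admitted, and any percentage is an assumption. A reader might infer that most emergency use will be missed, or that the inputs to the definitive trial will be materially too low. The article supports neither, because it gives no visit rate, admission share or unit cost.

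The conclusion rests on two assumptions: that the dataset's content follows its title, and that the linkage is requested as the article describes it. The effect is confined to the service-use and cost lines of a disaggregated analysis and to the economic inputs taken from them. It does not touch the feasibility criteria in section 1.1 or the PHQ-9. It is worth correcting because the correction is cheap and must be in place before the data are requested or collected.

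**What to change.** In section 2.9, keep the admitted-episodes dataset for inpatient stays and name a separate source that covers emergency visits without admission, if the agency can supply one. The article does not say whether it can, so this needs to be confirmed with the agency. The cost is one more extract in a linkage already planned.

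If no such source is available, make three linked changes:

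- Delete the emergency department from the linkage sentence in section 2.9.
- Add emergency department visits to the self-report items in section 4.2 at weeks 10 and 26.
- State in sections 2.9 and 4 that this self-report is the economic source for emergency visits.

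The cost is one question at two time points. It brings some recall error, since the recall periods would be 10 weeks and then 26 − 10 = 16 weeks, and answers would be available only for those who complete each assessment.
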